**IV.2.d. Postoperative follow-up**

All patients included will be followed in accordance with the guidelines for patients operated for CLM. Within the framework of this study, the patients will be followed during 30 days after the surgical operation.

### IV.3. Monitoring

#### IV.3.a. Common assessment to all phases

|                                                                                                                                  | INCLUSION                | PERIOPERATIVE            | POSTOPERATIVE            | 30 JOURS POST OPERATION  |
|----------------------------------------------------------------------------------------------------------------------------------|--------------------------|--------------------------|--------------------------|--------------------------|
|  WRITTEN CONSENT (SIGNED AND DATED)                                                                      |  |                          |                          |                          |
|  PREGNANCY TEST & IF NEEDED PRESCRIPTION OF A RELIABLE MEAN OF CONTRACEPTION (WOMEN OF CHILDBEARING AGE) |  |                          |                          |                          |
|  PERIOPERATIVE CT-SCAN (WITH PRECISE METASTASES SIZES IN PHASE IIb)                                      |  |                          |                          |                          |
|  CLINICAL CHECK-UP                                                                                       |  |                          |                          |                          |
|  NO EVIDENCE OF HURT IN NEARBY ORGANS                                                                    |                          |  |  |  |
|  HEMODYNAMIC VITAL SIGNS                                                                                 |                          |  |                          |                          |
|  RESPIRATORY VITAL SIGNS                                                                                 |                          |  |                          |                          |
|  BODY TEMPERATURE                                                                                        |                          |  |                          |                          |

#### IV.3.b. Phase I

|                                                                                                                                                                                                                                  | INCLUSION | PERIOPERATIVE                                        | POSTOPERATIVE                                        | 30 JOURS POST OPERATION |
|----------------------------------------------------------------------------------------------------------------------------------------------------------------------------------------------------------------------------------|-----------|------------------------------------------------------|------------------------------------------------------|-------------------------|
|  SHOOTINGS FEASIBILITY 
 
• ON SURFACE
 
• IN DEPTH
 
                                                                                                |           | 
 |                                                      |                         |
|  DURATION 
 
• OF OVERTIME NEEDED TO PERFORM 2 HIFU SHOOTINGS
 
• OF EACH SHOOTINGS STEP (INITIALIZATION, PROBE CONDITIONING, TARGETING, SHOOTING)
 
 |           | 
 |                                                      |                         |
|  ASEPSIS                                                                                                                                                                                                 |           |                              |                                                      |                         |
|  POSSIBILITY TO GENERATE A HIFU HURT IN AT LEAST 80% OF THE TOTAL LIVER                                                                                                                                  |           |                              |                                                      |                         |
|  POSSIBILITY TO : 
 
• SET A STATIONARY MARK
 
• MARK A VESSEL WITH PATENT BLUE OR METHYLENE BLUE
 
                                                  |           | 
 | 
 |                         |
|  FEASIBILITY OF REAL-TIME MONITORING OF THE HIFU IMPACT USING AN ECHOGRAPH COMBINED WITH THE MD                                                                                                          |           |                              |                                                      |                         |
|  FEASIBILITY OF HURTWITH EARLY ANATOMOPATHOLOGICAL DESCRIPTION                                                                                                                                           |           |                                                      |                              |                         |
|  FEASIBILITY TO MEASURE DISTANCE BETWEEN THE MARK / MARKED VESSEL AND THE HURT LIMITS DURING ANATOMOPATHOLOGICAL ANALYSIS                                                                                |           |                                                      |                              |                         |

#### IV.3.c. Phase IIa

|                                                                                                                                                                                                                  | INCLUSION | PERIOPERATIVE            | POSTOPERATIVE                                        | 30 JOURS POST OPERATION |
|------------------------------------------------------------------------------------------------------------------------------------------------------------------------------------------------------------------|-----------|--------------------------|------------------------------------------------------|-------------------------|
|  DISTANCE BETWEEN 

• HURT EPICENTRE / MARK (STEP 1)

• HURT LIMITS AND MARKED VESSEL BORDERS (STEP 2)

                              |           |                          | 
 |                         |
|  CORRELATION BETWEEN HURT MEASURES TROUGH 

• ECHOGRAPHY COUPLED TO THE MD

• ANATOMOPATHOLOGICAL ANALYSIS RIGH AFTER THE OPERATION

 |           |  |                              |                         |

#### IV.3.d. Phase IIb

|                                                        | INCLUSION | PERIOPERATIVE            | POSTOPERATIVE            | 30 JOURS POST OPERATION |
|--------------------------------------------------------|-----------|--------------------------|--------------------------|-------------------------|
|  SHOOTINGS AMOUNT / METASTASIS |           |  |                          |                         |
|  ANATOMOPATHOLOGICAL ANALYSIS  |           |                          |  |                         |

#### IV.4. Exclusion criteria during the study

A patient can be excluded of the study for one or several reasons:

- On sponsor or investigator decision,
- Withdrawal of his or her consent, or opposition to receive treatment,
- Inability to continue study (impossibility to carry out the hepatectomy, perioperative contraindication, intercurrent disease, worsening of clinical state, administrative reasons...)
- No news of the patient (lost to follow up),
- Patient's death.

Except in the last 2 cases, a final evaluation must be done, establishing the reasons why patient has to be dropped out.

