#### ✓ **Primary objectives**

To estimate:

- Hifu shootings **feasibility**,

↳ Through :

- 1) Ability to shoot :

- On the surface of the liver : in this case the hurt will start from the Glisson capsule and be extended to the subjacent parenchyma, and
- In DEPTH: In this case the hurt will be located in deeper parenchyma, at least 10 mm deeper than surface hurts.

- 2) The supplementary duration of intervention for 2 shootings given in minutes includes:
  - a. time to initialize the MD in operating room;
  - b. probe conditioning with acoustic coupling liquid;
  - c. time to define the target (x2) ;
  - d. time to deliver a shooting (x2).

The overtime caused must not exceed 30 minutes.

NB : Step a. and b. above-mentioned can be done in parallel to surgery. As far as they do not increase the duration of the surgical operation, they will not be taken into account. Same for the subsidiary research acts such as implanting marks.

- **Safety** using the MD,

↳ Through :

- 1) Capability to use the MD following requested asepsis procedures ,
- 2) No evidence of hurt on peripheral tissues (Glisson capsule on the opposite side of the HIFU shootings entrance area, retro-peritoneal, retro-hepatic tissues and diaphragm).

NB : it is possible that the Glisson capsule ultrasound hurts on the entrance area, that will be notified but not considered as a failure.

- HIFU shootings **tolerance**,

↳ Through: Ability to keep vital signs stable (hemodynamic, respiratory, body temperature) during shooting phase and the following 5 minutes.

 Hemodynamic vital signs : heart rate (HR), blood pressure (BP), heart flow (HF), by measuring the area under the curve on the Vigleo (N°3) monitor.

A significant alteration of vital signs will be defined as, at least, a 10% modification of one of these parameters compared to its value prior shootings.

✓ **Secondary objectives**

To determine :

- **Probe ergonomics** and feasibility of **area targeting**,
  - ↳ Through : Ability to adjust the probe position to different liver segments and patient physical structure. The aim is to be free to generate a HIFU hurt in at least 80 % of the total liver volume.
- Feasibility to set a mark (mark to estimate shootings accuracy in phase IIa-step 1),
  - ↳ Through : Possibility to set a stationary mark, at given depth, ecographically detectable,
- Feasibility to spot a specific vessel (used to estimate shootings targeting accuracy in phase IIa-step 2),

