#### VI.1.a. Phase I

**A group of 6 patients** will be included, in a sequential analysis divided into 2 steps following Lee's criteria (29). This analysis aims to stop prematurely the study if a failure rate  $> 15\%$  is observed.

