#### STATISTICAL RULES :

A failure is defined by at least one of the following situations:

- Overtime caused by shootings for 2 hurts exceeding 30 minutes,
- Impossibility to perform shootings on surface and/or in depth,
- Failing to respect requested asepsis procedures while setting the MD,
- Accidental hurt of nearby organs,
- Significant alteration of vital signs of at least  $10\%$  from its original value prior to the shootings.

[figure not shown]

To proceed to phase II will require to have fulfilled the following rule:

- 1st analysis after 2 patients:
  - If  $< 2$  failures are noticed  $\rightarrow$  continuation of the study and inclusion of 4 new patients,
  - If 2 failures the study is stopped.
- 2nd analysis after 6 patients:
  - If  $< 3$  failures are noticed  $\rightarrow$  continuation of the study and beginning of phase II (with Steering Committee's consent),
  - If  $\geq 3$  failures  $\rightarrow$  study is stopped.

NB: At the conclusion of the phase IIa, the Steering committee of the study will meet to examine all the brought together data, validate or not the criteria of continuation of the study and define more exactly the methodology of the phase IIb.

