## **VI.2. Definition of the studied population**

In each phase, the primary and secondary endpoints analyses will concern the population assessable for clinical feasibility, tolerance and accuracy to target CLM with HIFU. This population will consist in all patients included and which could have undergone a hepatectomy. Only those which could not have will be dropped out.

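### A patient harmed by the HIFU shots whose resection is then abandoned is a phase I failure, yet IV.4 and VI.2 together take that patient out of the assessable population

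*Protocol*

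**What the plan says.** Five places in the protocol bear on this.

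- **IV.4 (exclusion during the study).** Reasons for leaving include "On sponsor or investigator decision", withdrawal of consent, and inability to continue. The last covers a hepatectomy that cannot be carried out, a perioperative contraindication and a worsening clinical state. Loss to follow-up and death complete the list. No distinction is made between leaving before and after the first shot. On the exit assessment: "Except in the last 2 cases, a final evaluation must be done, establishing the reasons why patient has to be dropped out".
- **VI.2 (studied population).** In each phase, primary and secondary endpoints are analysed in included patients who could have the hepatectomy. "Only those which could not have will be dropped out". The synopsis puts it more directly: included patients who had a hepatectomy.
- **IV.2.c (surgical procedures).** The shots are given once the liver is freed and the indication checked, before any step specific to resection.
- **VI.1.a (phase I rules).** A failure is any one of: overtime above 30 minutes, inability to shoot at the surface or in depth, a breach of asepsis, accidental injury of a nearby organ, or a change in vital signs of at least 10%. After 2 patients: "If 2 failures the study is stopped". After 6, fewer than 3 failures continues and 3 or more stops.
- **IV.3.a (assessment schedule).** The item "NO EVIDENCE OF HURT IN NEARBY ORGANS" is due perioperatively, postoperatively and at day 30.

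**The concern.** The order of events lets a failure remove itself. The patient is exposed to the device first and qualifies for analysis second. Two of the five failure components, altered vital signs and injury of a nearby organ, are also events that could lead the team to abandon the resection. IV.4 then offers a matching exclusion reason, and VI.2 drops the patient because no hepatectomy took place.

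This is a first-in-human device study. II.3 names injury to surrounding organs as the principal risk, and the gate in question opens phase II. A rule that can omit the worst intraoperative outcome biases that gate in one direction only, towards continuing. The same population rule governs the safety and tolerance analyses of phases IIa and IIb.

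**Working it through.** **Step 1: the protocol's own boundary.** Inputs from VI.1.a: reference failure rate 15%, looks after 2 and 6 patients, stop at 2/2 or at 3 or more of 6. Taking the boundary as the smallest count whose one-sided 95% Clopper-Pearson lower limit exceeds 15%:

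- after 2 patients: 1/2 gives 2.5% and 2/2 gives 22.4%;
- after 6 patients: 2/6 gives 6.3% and 3/6 gives 15.3%.

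The matching tail probabilities at 15% are P(X≥2 | n=2) = 0.0225 and P(X≥3 | n=6) = 0.0473. The boundary reproduces, so the cut-offs are sound. The question is who is counted.

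**Step 2: following one patient through the text.**

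1. The shots are fired before resection (IV.2.c).
2. Vital signs change by at least 10%, or a nearby organ is injured: a failure (VI.1.a).
3. The resection is abandoned: a listed reason for exclusion (IV.4).
4. There was no hepatectomy, so the patient is dropped from the primary endpoint analysis (VI.2).

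The phase I primary criteria in III.1 are what the failure list counts. The phase I table in IV.3.b and the common table in IV.3.a place all of these checks in the operating room, with later checks for nearby organs only. None of the five components is defined by the resected specimen, so the hepatectomy requirement serves no purpose for them.

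**Step 3: effect on the decision.** Suppose 3 of 6 treated patients fail and one of the three was not resected.

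- Counted: 3/6, stop.
- Dropped without replacement: 2/5 (lower limit 7.6%), continue.
- Dropped and replaced by a patient without failure: 2/6, continue.

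At the first look, 2/2 stops; with one of the two dropped, the count cannot reach 2.

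**Step 4: illustrative size.** The protocol gives no rate for abandoned resection after HIFU and no replacement rule. Assume exactly one patient is such a failure and the others each fail independently with probability p. The chance of continuing is the sum, over first-look counts below 2, of P(first-look count) × P(total below 3).

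Worked at p = 0.30 with the affected patient among the last four:

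- counted as a failure: 0.49 × 0.784 + 0.42 × 0.343 = 0.528;
- dropped, not replaced: 0.49 × 0.973 + 0.42 × 0.784 = 0.806.

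Among the first two:

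- counted: 0.70 × 0.6517 = 0.456;
- dropped, not replaced: 0.70 × 0.9163 + 0.30 × 0.6517 = 0.837.

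If the patient is dropped and replaced, the result is the ordinary six-patient figure: 0.49 × 0.9163 + 0.42 × 0.6517 = 0.723.

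| p in the other patients | Counted as failure | Dropped, not replaced | Dropped and replaced |
|---|---|---|---|
| 15% | 0.757 / 0.835 | 0.973 / 0.960 | 0.941 |
| 30% | 0.456 / 0.528 | 0.837 / 0.806 | 0.723 |
| 50% | 0.156 / 0.188 | 0.500 / 0.469 | 0.328 |

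In each pair the first figure is for an affected patient among the first two, the second for one among the last four. The 15% rate is the protocol's reference; 30% and 50% are assumptions.

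**The case against.** Much can be said in the plan's defence.

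- **VI.2 governs the analysis, not IV.4.** A resected patient whom the investigator later excludes, or who dies or is lost, stays in the analysed population. This stands, and it confines the defect to patients shot but not resected.
- **Safety capture does not rest on the IV.4 exit evaluation.** That evaluation is described as establishing why the patient left. The abdominal cavity is explored during the operation (IV.2.c), all adverse events are recorded and followed (V.1.a), and severe events are reported from consent to day 30 whether or not related (V.1.b). This also stands.
- **Abandonment should be uncommon.** II.3 places the shots after the final check of the indication and immediately before resection. That is fair, but uncommon is not excluded, and IV.4 itself foresees it.
- **The gate has a human check.** Opening phase II needs the Steering Committee's consent, and II.3 has an independent committee consider all results. That reduces the risk, but does not tell the committee whom to count.
- **VI.1.a speaks of patients without citing VI.2.** One could therefore count everyone treated. The protocol does not say so, and VI.2 claims the primary endpoints of each phase.

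A reader might go further and infer from the wording "No evidence of hurt on peripheral tissues" that an unassessed patient passes by default. The protocol does not support that. No section scores missing data as a pass, the gate counts accidental injury as an event, and the nearby-organ item is scheduled three times. Nor should the table be read as the effect of loss to follow-up: four of the five components are settled in the operating room, and resected patients stay in the analysis.

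**Conclusion.** The point holds in a narrow form. Because exposure precedes the event that defines the analysis population, a failure caused by the device can take itself out of the phase I count. It changes the decision only at the boundary: three failures among six, or two among the first two, with the unresected patient among them. With so small a gate, that is one patient.

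The probabilities are conditional illustrations. They assume that one such patient occurs, that the others fail independently at a common rate, and that VI.2 defines who enters the gate. How often this would happen cannot be judged from the protocol.

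The waiver of the exit evaluation for death and loss is a lesser matter. It leaves unstated how the day-30 nearby-organ item is completed for those patients, but it does not turn missing data into successes. The whole can be corrected by wording before enrolment and is worth correcting.

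**What to change.** 1. In IV.4 and VI.2, and in the matching synopsis paragraph, state that every patient who receives at least one HIFU shot stays in the phase I failure count and in the safety and tolerance analyses of all phases, whether or not hepatectomy follows and whatever the later reason for leaving.
2. Limit the hepatectomy requirement to endpoints that need the resected specimen, such as the distances in phase IIa and the margins in phase IIb.
3. Require the nearby-organ item for every patient shot, including those who die or are lost, from existing operative, re-intervention and hospital records. Report unknown day-30 status as not assessed, with a sensitivity count beside the main one.

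Scoring every unknown as a failure is not proposed. At a 15% failure rate, one unobserved patient scored that way would cut the chance of continuing from 0.941 to 0.757–0.835, a heavy price for a gate of six.

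The cost is a few sentences and one case report form item. Sample size, cut-offs and procedures are unchanged. The drawback is that a patient whose resection is abandoned for a reason unrelated to the device still takes one of the six places, and supplies no specimen for the secondary pathology objectives.

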#### IV.5. Premature end of the study

The study can end prematurely due to administrative reasons, or if new elements come up and reveal an unbalanced benefit / risks ratio, and/or on sponsor or statutory authorities decision.

If the study ends prematurely or has to be suspended, the sponsor will immediately inform the investigators, statutory authorities and the CPP why. Whatever happens during the study, a follow-up has to be achieved by the investigator

## **V. SAFETY**

---

The CLB is represented by the Lyon Regional Pharmacovigilance Centre (RPC) for the safety in clinical trials for which it is the sponsor.

### **V.1. Notification of adverse events by investigators**

#### **V.1.a. Notification of adverse events in the case report form**

Any intercurrent clinical or biological event, either severe or not, happening at anytime of the study, being related to research or not, must be written in the dedicated part of the case report form (CRF)  
All intercurrent events, of any severity, must be followed by investigator until total remission or at least stabilization of the adverse event.

#### **V.1.b. Notification of severe adverse events to the sponsor**

The investigator will immediately inform the sponsor about all Severe Adverse Events (SAE) occurring in patients included or among users of the MD during the study period (except for those mentioned hereunder), in a notification form, the SAE being considered imputable to research or not. The initial notification must be promptly followed by one or several supplementary detailed statement(s).

Any SAE occurring in patients included must be stated from the date of the written consent until 30 days after surgery (being the end of the planned follow-up period), without time limits if investigator thinks that the event is likely to be related to the experimentation.

#### **V.1.c. Adverse events not to be reported immediately**

**Non severe events:** Less than 24 hours hospitalisation.

**Events not related to MD experimentation:** planned hospitalisation prior to the study start.

NB: If isolated, these events do not require to be immediately notified to sponsor, but need to be reported in the CRF.

#### **V.1.d. Adverse events related to the pathology or the surgery**

**SAE related to colorectal metastatic cancer:** digestive haemorrhage associated with anastomosis, perianastomotic abscess, digestive fistula, persisting post operative ileus...

**Complications specific to liver metastases surgery:** Bleeding from the hepatectomy resection, clinical or biological liver insufficiency (increased bilirubin above 50µmol/L and decreased prothrombine beneath 50 % after the fifth day post operation), ascites, icterus, portal hypertension signs, persistent biliary fistula...

